### Randomisation and Blinding

After baseline data collection, the 30 practices are randomly allocated in variable blocks (stratified by DGP) to 'intervention' or 'control' groups by a person independent of the research team using computer generated random numbers. Staff involved in the data collection are independent of those involved in the intervention and are not informed which practices are randomized to intervention or control groups.

### Intervention

The main aim of the intervention is to assist high risk patients to make positive lifestyle changes through supporting self-management knowledge and skills, providing social support and increasing self-efficacy. At the practice level, this includes training practice staff in assessing risk factors and motivational interviewing using simulated consultations with actors and practice support. Patient education resources include resources from the Lifescripts program [27], patient waiting room questionnaires, a Health check visit guide, a checklist for GPs to complete when they see patients, and a food diary (patients are asked to fill out 3-4 days of their diary intake each week, including at least one weekend day, in the Daily Living Diary provided).

At the patient level, the goals of intervention are based on those used in previous diabetes prevention studies, including the U.S. Diabetes Prevention Program (DPP) and the Finnish Diabetes Prevention Study (DPS) [6,7,9] (Table 3).

**Table 3 T3:** HIPS intervention goals

	Intervention Goals
Exercise	• Moderate exercise for at least **30 minutes/day**, including walking, jogging, swimming, aerobics, ball games, or skiing with circuit-type resistance training, twice a week.

Diet	• Diet low in saturated fats, sucrose and salt with increased portions of vegetables and fruit per day (up to 7 portions) in order to achieve a diet with the percentage of energy from carbohydrate = 50%, saturated fat < 10% and total fat < 30%, protein 1 g/kg ideal body weight per day, fibre 15 g/1000 kcal.

Weight reduction	• (if overweight) of ≥ 5 kg or 5% of body weight

Smoking cessation	• if smoker

Limit alcohol intake	• (if drinking) to ≤ 2 drinks/day, including 1-2 alcohol free days/Week

#### GP/PN brief intervention

This intervention is modelled on previous research conducted by the investigators, called SNAP (Smoking, Nutrition, Alcohol, Physical activity) interventions in general practice [22], and evaluation of the 45-49 year health check [28]. The aim is to develop a brief intervention that can be carried out by busy GPs and their practice staff at the time of a "health check" such as that currently supported for patients aged 45-49 years [29] (Table 4). The key theoretical underpinning for the GP intervention is the Trans-theoretical (Stages of Change) Model which focuses on the assessment of patient readiness to change and stage-based tailoring of brief behavioural counselling [30]. This is applied within the framework of the 5As model [31] (Table 5). A broad definition of high risk (Table 6) is used (presence of a physiological risk factor, overweight or smoking).

**Table 4 T4:** HIPS Health Check Visit

Health Check Visit - checklist
• SNAP lifestyle risk factor assessment and assessment for previous GDM
• Review of pathology reports (lipids, fasting glucose) and/or ordering of these
• Physical assessment (weight, height, BMI, waist circumference)
• Assessment of readiness to change
• Interventions offered (education, medication change)
• Referral of high risk patients for nutrition/physical activity program
• Follow up visit with GP at about 10 - 12 weeks

**Table 5 T5:** 5As model

Ask	Identification of eligible patients who are 40-64 years from practice records with invitation to attend the practice for a health check following a blood test for fasting glucose and lipids. Completion of a waiting room questionnaire by patients on their risk factors
**Assess**	Assessment of behavioural and physiological risk factors and readiness to change

**Advise**	Brief advice using written materials (lifescript resources)

**Assist**	Motivational counselling and medications if appropriate

**Arrange**	Referral of high risk patients who are unsure or are ready to change to an allied health provider (either an exercise physiologist or a dietician) for individual advice and goal setting; and to the *CHANGE for HIPS *group program. Prior to attending the program patients are asked to complete a food diary. Follow up is arranged with the GP at about 10 - 12 weeks.

**Table 6 T6:** Definition of high risk patient

Definition of High Risk patient
High risk patients are defined as those with any of the following characteristics:
• have history of gestational diabetes (GDM)
• have 'Pre diabetes' - (impaired glucose tolerance or impaired fasting glycaemia)
• have elevated blood pressure (BP ≥ 140/90 on two occasions) or on treatment for high blood pressure
• have high Lipid: Total Cholesterol (TC) > 4.5 mmol/L or Low Density Lipoprotein (LDL) > 2.5 mmol/L or Triglyceride (TG) > 2.0 mmol/L or on treatment for it
• are overweight: BMI > 28 or waist circumference > 102 cm in males and 88 cm in females
• currently smoke.

#### Development of the Intervention Program for High Risk Patients

##### Individual lifestyle sessions

Patients at high risk are asked to attend an initial visit, at which an allied health practitioner (AHP) reviews their food diary and negotiates individual dietary and physical activity goals with the patient. A follow-up visit with the AHP is arranged at around 8-9 weeks to review progress and negotiate additional dietary and physical activity goals.

##### Group Lifestyle Education - CHANGE for HIPS

After attending the AHP, patients are enrolled the *CHANGE for HIPS*, This is a group education program, which is adapted from the group component of the "*Counterweight Program - CHANGE*" in the UK [32]. An intervention officer (IO) from the local DGP is trained to facilitate this program and provided with the required resources. *CHANGE for HIPS *consists of four group sessions (1.5 hours each) over the first three months and a further two follow-up sessions at six and nine months. The group sessions include an educational and physical activity component (20-30 minutes of walking or resistance exercise) and are based on the use of self-management strategies (goal setting, selfmonitoring, and developing practical skills and problem solving to promote positive dietary and physical activity changes and weight loss) (Figure 2). Between sessions patients keep a food and physical activity diary, use a pedometer and carry out home-based physical activity.

**Figure 2 F2:**
[figure not shown]
**CHANGE for HIPS**.

#### Quality assurance

The quality of the intervention process is monitored by an Intervention Advisory Committee It includes evaluation of the GP/PN training sessions, evaluation of group sessions in each DGP, record of practice visits kept by IOs and ongoing feedback by practice staff on the intervention, and evaluation of patients' feedback on group sessions.

#### Usual care

Patients attending the control practices receive usual general practice care of their risk factors. After the second data collection at 12 months, the HIPS GP/PN training is offered to GPs in those practices.

### Data collection

Data are collected at baseline, 6 months and 12 months from administrative staff, GPs, PNs, and patients. The questionnaires take between 10-30 minutes to complete (Table 7). These questionnaires have been piloted before their use in the trial.

**Table 7 T7:** Study instruments

Measurement	Details	Timeframe
**Practice questionnaire (PPVQ)**	• Practice capacity for preventive care including use of patient education materials, staff roles and teamwork in preventive care, and linkages between the practice and support services	**Baseline**

**GP/PN survey**	• This survey is based on questions from the *Preventive Medicine Attitudes and Activities Questionnaire (PMAAQ) *[38], and the *Vascular Interventions Survey *[39]	**Baseline & 12 Month**

**Patient's survey**	• This survey is based on the NSW Health Survey and previous research [40,41]. It includes questions about: (1) Practice attendance; (2) reported assessment and management of SNAP risk factors; (3) attendances at other services as a result of referral from the practice or self-referral; (4) self-reported fruit and vegetable intake, smoking, physical activity and alcohol intake, and attempts to change these; (5) readiness for behaviour change (stage of change) for each SNAP risk factor [42]; (6) The Kessler Psychological Distress Scale (K-10), a ten item questionnaire measuring negative emotional states in the preceding four weeks [43]; (7) The Neuroticism Scale from the Eysenck Personality Questionnaire Revised, Short form (EPQ-N-RS) [44], which represents an individual's tendency to experience psychological distress or neuroticism; (8) satisfaction with their care, using the General Practice Assessment Questionnaire (GPAQ) which includes questions in relation to satisfaction with GP and AHP visit and health check [45]	**Baseline & 6 months & 12 month**

**Patient's physical assessment**	• Includes weight, height, BMI, waist circumference and blood pressure measurement.	

**Patient's fasting blood tests**	• Patients are asked to have a fasting blood test to assess their serum lipids (total cholesterol, HDL, LDL, triglycerides) and glucose.	**Baseline & 12 month**

**Clinical record audit**	• Patient records are examined to determine recorded weight, waist circumference, blood pressure, practice attendances during the 12 months of the trial, referral to interventions to address risk factors identified, prescribing of medications (lipid lowering and antihypertensive medications), referrals to dietician, exercise and smoking cessation program.	**12 month**

**GP/PN & IOs interviews**	• Qualitative interviews are conducted with GPs and PNs in the intervention group and with IOs to explore experience of implementing SNAP risk factor management in routine practice, feasibility and acceptability of brief lifestyle intervention, as well as acceptability and usefulness of referral to support services.	**12 month**

#### Sample size calculation

All sample size calculations use a significance level of 5% and power of 80%, with design effects and estimated expected differences between the intervention and control groups based on previous research

##### Evidence-based intervention provided to patients

Assuming a design effect due to clustering of 2 based on previous studies [30-33], a sample of 188 patients in each group will detect a 20% difference in the proportion of patients offered evidence-based interventions (motivational counselling or referral to appropriate services) to modify their risk factors, compared to the control group.

##### Reduction in physiological risk factors

Assuming a design effect due to clustering of 1.8, loss to follow up of 20% and standard deviations based on data from general practice diabetes registers [34]:

• weight: assuming a standard deviation of 19, a sample size of 382 will be sufficient to detect a mean difference of 4 Kg in weight between intervention and control groups.

• LDL cholesterol: assuming a standard deviation of 0.9, a sample size of 342 will be sufficient to detect a mean difference of 0.2 mmol/L in LDL-cholesterol between intervention and control groups.

• blood pressure: assuming a standard deviation of 11, a sample size of 228 will be sufficient to detect a mean difference of 3 mmHg in systolic blood pressure between intervention and control groups.

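### The weight, LDL and systolic blood pressure sample sizes omit the factor of 2 for a two-group comparison; on the stated inputs they give about 49% power, not 80%

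*Protocol article*

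**What the plan says.** The Protocol article, *Sample size calculation*, sets one standard for every calculation: "All sample size calculations use a significance level of 5% and power of 80" per cent.

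The subsection *Reduction in physiological risk factors* adds its inputs, "Assuming a design effect due to clustering of 1.8, loss to follow up of 20" per cent, and describes its "standard deviations based on data from general practice diabetes registers". It then gives three sizes, each for a mean difference between the two arms:

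- Weight: "assuming a standard deviation of 19, a sample size of 382 will be sufficient to detect a mean difference of 4 Kg in weight".
- LDL cholesterol: "assuming a standard deviation of 0.9, a sample size of 342 will be sufficient to detect a mean difference of 0.2 mmol/L".
- Systolic blood pressure: "assuming a standard deviation of 11, a sample size of 228 will be sufficient to detect a mean difference of 3 mmHg".

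These three bullets do not say whether the sizes are per group or in total. The neighbouring subsections, on evidence-based interventions and on behavioural risk factors, do say that theirs are per group. At the end of the behavioural subsection the article plans for 600 patients enrolled per group, 480 after loss, and 288 of those at high risk. Weight, LDL and blood pressure are the physiological outcomes of hypothesis 3, which Table 1 lists as primary and which concerns high-risk patients.

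**The concern.** The inputs and outputs are all printed, so the sizes can be checked directly, and they are about half of what a comparison of two means requires. If the factor of 2 was left out, a primary hypothesis is presented as having 80% power for weight, LDL and blood pressure when the stated assumptions give roughly an even chance of detecting the target differences. A non-significant result could then be read as evidence against an effect of that size when the trial was not large enough to support that reading.

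**Working it through.** **Inputs.** From *Sample size calculation*: alpha 0.05 (two-sided assumed, as sidedness is not stated) and power 0.80, so (1.960 + 0.842)² ≈ 7.849. From *Reduction in physiological risk factors*: design effect 1.8; loss 20%; SD and difference d of 19 and 4 kg, 0.9 and 0.2 mmol/L, 11 and 3 mmHg. Equal groups are implied by the recruitment plan.

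**Step 1: reproduce the stated sizes.** The single-mean formula is n = 7.849 × SD²/d². Multiply by 1.8 for clustering and by 1.2 for loss.

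| Outcome | Single-mean n | × 1.8 × 1.2 | Stated |
|---|---|---|---|
| Weight | 177.1 | 382.5 | 382 |
| LDL | 158.9 | 343.3 | 342 |
| Systolic BP | 105.5 | 227.9 | 228 |

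All three agree to within about one patient. The two-group formula does not reproduce them with any combination of the two inflation factors. To reach the stated sizes from it, the combined inflation for clustering and loss would have to be about 1.08 (382/354.2), whereas the stated inputs require 1.8 × 1.2 = 2.16 or 1.8/0.8 = 2.25.

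**Step 2: the two-group requirement.** n per group = 2 × 7.849 × SD²/d². Multiply by 1.8 for the number analysed, then divide by 0.8 for the number enrolled.

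| Outcome | Before inflation | Analysed (× 1.8) | Enrolled (÷ 0.8) | Rounded up |
|---|---|---|---|---|
| Weight | 354.2 | 637.5 | 796.9 | 797 |
| LDL | 317.9 | 572.2 | 715.2 | 716 |
| Systolic BP | 211.0 | 379.9 | 474.9 | 475 |

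Multiplying by 1.2 is also a small error in its own right. To retain n after 20% loss one divides by 0.8, that is, multiplies by 1.25.

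**Step 3: power at the stated sizes.** Take them as per group, the more favourable reading. The effective n per group is m = stated × 0.8/1.8, and power = Φ(d/(SD√(2/m)) − 1.960).

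- Weight: m = 169.8; 4/2.062 = 1.940; power 49.2%.
- LDL: m = 152.0; 0.2/0.1032 = 1.937; power 49.1%.
- Systolic BP: m = 101.3; 3/1.545 = 1.941; power 49.3%.

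Undoing the loss by dividing by 1.2 instead gives about 51%. If the sizes were totals, power would be about 28%.

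**Step 4: power at the planned recruitment.** With 288 analysed high-risk patients per group, m = 288/1.8 = 160, and power is 46.9% (weight), 51.1% (LDL) and 68.4% (systolic BP). If all 480 completers per group were analysed, it would be 68%, 73% and 88%.

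**Step 5: what 288 per group can detect at 80% power.** d = SD × √(2 × 7.849/160) = SD × 0.313, which is about 6.0 kg, 0.28 mmol/L and 3.4 mmHg.

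**Step 6: correlation that would rescue the stated sizes.** If baseline adjustment reduces the variance by (1 − ρ²), 80% power needs 1 − ρ² = m/(two-group n before inflation). For weight this is 169.8/354.2 = 0.479, so ρ = 0.72. LDL and systolic BP also give 0.72. With loss taken as ÷ 1.2, ρ is about 0.71.

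**Step 7: is it a convention used throughout?** No. The 188 per group for the offer of evidence-based interventions, with design effect 2, fits the two-group formula if 40% against 60% is assumed: 2 × 7.849 × (0.24 + 0.24)/0.2² = 188.4. Those proportions are an assumption, as the article does not give them.

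**The case against.** The strongest reply is that the factor of 2 may have been offset on purpose. Halving the two-group size is what a baseline-adjusted analysis with a correlation near 0.71 would yield, or a change-score analysis with a correlation of 0.75. The subsection is about reductions, hypothesis 3 is framed as change over 12 months, and the *Data Analysis* section does plan adjustment for baseline differences. A condensed article might leave the correlation to the full protocol. It follows that 49% is the power of an unadjusted comparison on raw SDs, and that power under the planned adjusted analysis cannot be determined from the article.

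That qualification stands: a high correlation is possible, especially for weight, and would raise power. It does not rescue the printed calculation. The subsection lists its assumptions and includes neither a correlation nor a change-score SD; its SDs come from registers. The same correlation would also have to apply to three different outcomes, whereas the omitted factor explains all three sizes at once. That the omission is the cause is an inference; that the sizes do not follow from the stated two-group inputs is certain.

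It can also be said that these bullets do not set recruitment, which is built from practices, invitations and response. That is true and limits the consequence to the justification, but the planned 288 per group falls short of 80% for all three outcomes. The total-sample reading (28%) is the less likely one, given the per-group wording nearby, and the loss-inflation error moves power by only about two percentage points.

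**Conclusion.** The point holds. The stated sizes of 382, 342 and 228 are about half the per-group requirement of a two-group comparison on the article's own SDs, differences, design effect and loss. Read as per group, they give about 49% power (51% if loss is undone as ÷ 1.2) against the stated 80%. The planned 288 analysed per group give 47%, 51% and 68%. These figures assume two-sided 5% significance, equal groups and no variance reduction from baseline adjustment. Crediting a baseline correlation of about 0.72 for each outcome would bring the stated sizes to 80%, but the article makes no such assumption. Because the stated power of a primary hypothesis is overstated by about 30 percentage points, the text needs correcting.

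**What to change.** Correct the three bullets in one of these ways, and say explicitly that the figures are per group:

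1. Keep the recruitment target and state what 288 analysed high-risk patients per group can detect at 80% power on the raw SDs: about 6.0 kg, 0.28 mmol/L and 3.4 mmHg.
2. If the planned baseline-adjusted analysis is to be credited, state the assumed baseline-to-12-month correlation ρ for each outcome and its source, multiply the two-group size by (1 − ρ²), and report the resulting power at 288 per group.
3. Print the unadjusted two-group requirement: 797, 716 and 475 enrolled per group (638, 573 and 380 analysed, rounded up). For weight and LDL this exceeds the planned 600 enrolled per group, so it would have to be accompanied by the power actually available.

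The first or second suits the trial better, since neither implies a target that the recruitment plan cannot meet. Whichever is used, inflate for loss by dividing by 0.8. The cost is a change of text: no extra patients and no change to design or analysis, but a less favourable statement of power or of detectable difference.

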##### Reduction in behavioural risk factors

Assuming a design effect due to clustering of 1.8 and a 20% loss to follow up with estimates based on previous research [35]:

• if patients eat a standard deviation 2.1 portions of fruit and vegetables a sample of 288 in each group would have sufficient power to detect a mean 0.5 portion difference.

• if 22% smoke, a sample of 363 in each group would have sufficient power to detect a 6% difference.

• if 30% consume alcohol at risk levels, a sample of 362 in each group would have sufficient power to detect a 7% difference.

• For physical activity, a score of 2.1 in a sample of 305 in each group would have sufficient power to detect a mean 0.5 score difference.

We aim to recruit 30 general practices and identify 160 patients from each practice (total = 4800). From this we anticipate 25% responses in each group (600 patients in each group). An estimated 20% loss to follow-up will leave 480 patients in each group, of which we estimate 60% are high risk (288 patients in each group) (Figure 3).

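### On their own stated inputs the behavioural sample sizes do not give 80% power: about four times too small for smoking and alcohol, about two times for fruit and vegetables, and about two times for physical activity if its 2.1 is an SD

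*Protocol article*

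**What the plan says.** Under *Sample size calculation*, the protocol article sets one rule: "All sample size calculations use a significance level of 5% and power of 80" (per cent). Under *Reduction in behavioural risk factors* it adds: "Assuming a design effect due to clustering of 1.8 and a 20% loss to follow up with estimates based on previous research". Four claims follow:

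- Fruit and vegetables: "if patients eat a standard deviation 2.1 portions of fruit and vegetables a sample of 288 in each group" and "would have sufficient power to detect a mean 0.5 portion difference".
- Smoking: "if 22% smoke, a sample of 363 in each group would have sufficient power to detect a 6% difference".
- Alcohol: "if 30% consume alcohol at risk levels, a sample of 362 in each group would have sufficient power to detect a 7% difference".
- Physical activity: "a score of 2.1 in a sample of 305 in each group would have sufficient power to detect a mean 0.5 score difference".

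The same section expects 600 patients enrolled per group, 480 after loss, and 288 of those at high risk. Table 1 places diet, activity, smoking and alcohol in primary hypothesis 3, which compares high-risk patients between the groups. *Quantitative evaluation - statistical analysis* plans multilevel models with adjustment for baseline differences. No baseline correlation or variance reduction appears among the sample-size inputs.

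**The concern.** The section prints both its inputs and its answers, so the answers can be checked, and they do not agree. Detecting a drop of 6 points from 22%, or 7 points from 30%, takes more than 600 patients per group in an individually randomised trial with complete follow-up. Sizes of 363 and 362 cannot then also absorb a design effect of 1.8 and 20% loss. The fruit and vegetable figure of 288 is close to what is needed before any inflation, not after it.

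These four outcomes are four of the seven in primary hypothesis 3. A reader who takes the section at face value would read a non-significant smoking or alcohol result as coming from a test with 80% power for the stated difference.

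**Working it through.** **Inputs.** From the article: 5% significance, 80% power, design effect 1.8, 20% loss, sizes per group, and the rates, SD and differences quoted above. Assumed: a two-sided test (sidedness is not stated; z = 1.960 and 0.842); the hypothesised direction of benefit (22% to 16%, 30% to 23%); 2.1 is an SD for activity; no gain from covariates.

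**Attempt to reproduce the stated sizes.** One-sided testing, a continuity correction, an increase instead of a decrease, design effect only, loss only, multiplying by 1.2 instead of dividing by 0.8, and no inflation at all were each tried per group with the printed inputs. None comes within 3% of 288, 305, 363 or 362.

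**Required size.**

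Means: n = 2(1.960 + 0.842)² × 2.1² / 0.5² = 2 × 7.849 × 4.41 / 0.25 = 276.9. Then × 1.8 = 498.4, and / 0.8 = 623. An SD printed as 2.1 may lie between 2.05 and 2.15, which gives 594 to 653.

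Proportions: n = [1.960√(2p̄(1−p̄)) + 0.842√(p₁(1−p₁) + p₂(1−p₂))]² / (p₁−p₂)².

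- Smoking, p̄ = 0.19: (1.960 × 0.5548 + 0.842 × 0.5532)² / 0.06² = 669.9. Then × 1.8 = 1,205.8, and / 0.8 = 1,507.3, so 1,508.
- Alcohol, p̄ = 0.265: (1.960 × 0.6241 + 0.842 × 0.6222)² / 0.07² = 622.8. Then × 1.8 = 1,121.1, and / 0.8 = 1,401.3, so 1,402.

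| Outcome | No inflation | × 1.8 | / 0.8 | Stated | Ratio |
|---|---|---|---|---|---|
| Smoking | 670 | 1,206 | 1,508 | 363 | 4.15 |
| Alcohol | 623 | 1,121 | 1,402 | 362 | 3.87 |
| Fruit and vegetables | 277 | 498 | 623 | 288 | 2.16 |
| Activity (if SD) | 277 | 498 | 623 | 305 | 2.04 |

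**Power at the stated sizes.** If the sizes are enrolled, the effective number per group is m = stated × 0.8 / 1.8. If they are completers, m = stated / 1.8. Two examples, read as enrolled:

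- Fruit and vegetables: m = 128; 0.5 / (2.1√(2/128)) − 1.960 = 1.905 − 1.960 = −0.055, so 48%.
- Smoking: m = 161.3; (0.06√161.3 − 1.960 × 0.5548) / 0.5532 = −0.588, so 28%.

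The last two columns take 288 or 480 completers per group, with m = 288/1.8 = 160 or 480/1.8 = 266.7.

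| Outcome | Enrolled | Completers | No clustering, no loss | 288 high-risk completers | All 480 completers |
|---|---|---|---|---|---|
| Smoking | 28% | 34% | 54% | 28% | 42% |
| Alcohol | 29% | 36% | 57% | 29% | 45% |
| Fruit and vegetables | 48% | 57% | 82% | 57% | 79% |
| Activity (if SD) | 50% | 59% | 84% | 57% | 79% |

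**Other assumptions.** One-sided, read as enrolled: 39%, 41%, 60% and 62%. If the proportions rise (22% to 28%, 30% to 37%), smoking and alcohol fall to 24% and 26%.

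**What 288 analysed per group detects at 80% power (m = 160).** Means: 2.1 × √(2 × 7.849 / 160) = 0.66. Solving the proportions formula for n = 160 gives smoking 22% to about 10.5% and alcohol 30% to about 17%.

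**The case against.** **Baseline adjustment.** The strongest defence is that the planned analysis adjusts for baseline, which can reduce the required size. For continuous outcomes this matters: with a baseline correlation of 0.7 (illustrative; the article gives none), 288 fruit and vegetable completers would have about 85% power, because the SD becomes 2.1√(1 − 0.49) = 1.50. It does not rescue the section as written. As an approximation, closing the gap needs residual variance of 288/623 = 0.46 and 305/623 = 0.49 for diet and activity (correlation about 0.7), but 363/1,507 = 0.24 and 362/1,401 = 0.26 for smoking and alcohol (correlation about 0.86 to 0.87). No single unstated factor explains all four.

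**The bullet sizes are not the recruitment target.** This stands. The power of the planned trial depends on whom it analyses. Fruit and vegetables reach 57% in the high-risk comparison and 79% if all 480 completers are used, so the shortfall there is milder than 48% suggests. Smoking and alcohol stay at 45% or below.

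**Total instead of per group.** The text says each group. Halving the correct sizes gives 754 and 701 for smoking and alcohol, and 312 for diet and activity; only activity (305) is close.

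**Readings that go too far.**

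- A reader might infer that 288 and 305 contradict each other because both bullets show 2.1 and 0.5. They need not. Their ratio is 1.059, and rounding of the SD alone allows up to (2.15/2.05)² = 1.10.
- A reader might infer that the inflation was simply forgotten. That could fit 288, but 363 and 362 are below even the uninflated sizes. The article does not show how the error arose.
- A reader might take activity as a proven error. The article calls 2.1 a score and gives no SD, so that figure is conditional.
- A reader might conclude that null results would be uninformative. The trial could still report intervals; what fails is the claim of 80% power for the stated differences.

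**Conclusion.** The point holds. On the section's own inputs, with a two-sided test and no gain from baseline adjustment, the stated sizes are too small by a factor of about 4 for smoking and alcohol and about 2 for fruit and vegetables. Physical activity is too small by about 2 only if 2.1 is its SD.

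The 28% to 50% power range is not unconditional. It applies to an unadjusted two-sided test with the stated sizes read as enrolled; read as completers, the range is 34% to 59%. No reading tried that applies the stated design effect, without an unstated gain from adjustment, reaches 80%.

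The smoking and alcohol result is the firmest, because it does not depend on how clustering or loss is handled. The fruit and vegetable result depends on the inflation that the section itself says it applies. Because these figures support a primary hypothesis, they should be corrected.

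**What to change.** 1. Keep the recruitment target and restate what 288 analysed per group detects at 80% power with design effect 1.8: about 0.66 portions, smoking 22% to about 10.5%, risky alcohol 30% to about 17%.
2. State that smoking and alcohol are not powered for differences of 6 and 7 points.
3. Correct the bullets to match their stated assumptions: about 1,508 (smoking), 1,402 (alcohol) and 623 (fruit and vegetables) enrolled per group. The first two are more than twice the planned 600 per group, so they document the shortfall and are not a practical target.
4. Say what the 2.1 for physical activity is, give its SD, and recompute from that.
5. If any gain from baseline adjustment is relied on, state the correlation used for each outcome.
6. State whether the test is one- or two-sided and whether the sizes are enrolled or completers.

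The cost is text only. Design and recruitment are unchanged; the stated power becomes less favourable.
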